### Control Group

The control group follows the same conceptual procedure and sequence as the intervention group (Figure 1). Thus, they have the same number of individual sessions and accordingly receive same attention from the study staff. They also fill out all the questionnaires, give blood, and fill out the diary for the same amount of time. However, there are differences in the content of the sessions, in that the control group will not receive information about the circadian clock, its connection to addiction, and the importance of having a structured daily life. Instead, participants of the control group are given the opportunity to discuss, for example, the role of legal drugs, such as alcohol, in society and the effects of alcohol advertising and its impact on both individual and societal consumption behavior. Since the test persons of the control group do not receive any further instructions for the diary and are only asked to fill it in carefully, the evaluation of the study data provides the possibility to compare Routine Variability Scores of test persons of the intervention group and the control group.

## Measured Outcomes

Our primary hypothesis is that a regular exposure to *Zeitgebers* stabilizes circadian behavioral rhythms and thereby reduces the risk of alcohol relapses in AUD patients. Therefore, the first primary outcomes of the study are the Routine Variability Score and drinking behavior of each individual test person. For generation of the Routine Variability Scores, first, day-to-day variability will be calculated from the following parameters: bedtime, wake-up time, sleep quality, time of getting-up in the morning, time to go to bed in the evening, lights-off time, breakfast time, lunch time and dinner time. The individual Routine Variability Score is comparable to the validated social rhythm metric scale (SRMS) (66) and will be calculated as follows (example for bedtime): For the period of 1 week, the average bedtime will be calculated. Then the deviation from this average bedtime is calculated in minutes for each day. These deviations are summed up and the mean value is calculated. This mean value will be coded according to the magnitude of time variability: 1: 0–15 min, 2: 16–30 min, 3: 31–45 min, 4: 46–60 min, 5: 61–75 min, 6: 76–90 min, 7: 91–105 min, 8: 106–120 min, 9: 2–3 h, 10: 3–4 h, 11: over 4 h (67). This way a separate score can be created for each parameter collected in the diary. These scores can be calculated on a weekly basis to examine whether relapses or deterioration in well-being are related to irregularities in the daily routine during that week, or over the duration of the entire survey phase to check how regularity over a longer period is related to drinking behavior and well-being. In addition, the scores for sleep and meals, for example, can be calculated individually to examine their influence on drinking behavior and well-being separately.

Additionally, a questionnaire specially designed for this study with a total of 30 questions and a 4-step ordinal scale for the answers to assess the rating of the participants' subjective structuredness in their everyday life will be filled out. This questionnaire includes, for example, questions on the subjective assessment of whether activities such as eating, sleeping and sport are carried out regularly, whether relapses are associated with irregular daily routines, and whether the craving for alcohol usually occurs at the same time of day. To give the subjects of the control group no indication of the actual aim of the study, the questions that aim at the circadian daily structure are mixed with neutral questions.

Drinking behavior and daily craving will be assessed with questionnaires and the diary, respectively (Table 1). General drinking habits of the last few weeks are surveyed using the AUDIT questionnaire. In addition, the European Addiction Severity Index (EuropASI) is used, which covers not only alcohol and drug consumption but also physical, psychological, financial, and social problem areas of addicted patients. The number of alcoholic drinks and the number of alcohol-free days within the past 30 days is assessed by means of the Timeline Followback 30 (TLFB-30). The diary, which the subjects fill out to collect the Routine Variability Scores, additionally records the highest craving for alcohol on a scale of 0–10 of each day.

According to our secondary hypothesis that the stabilization of circadian rhythms contributes to the reduction of depressive symptoms and increased well-being, changes in the affective state, with a focus on depressive symptoms, are measured with the external assessment questionnaire Hamilton Depression Scale (HAMD) and with the self-reporting questionnaire Inventory of Depressive Symptomatology (IDS-SR). Sleep quantity and quality will be assessed by Pittsburgh Sleep Quality Index (PSQI). Furthermore, for measuring if the DAILY structure program will influence the feeling of self-efficacy, we will employ the Generalized Self-Efficacy Scale (GSES).

As exploratory outcomes, it will be documented how many subjects in the DAILY intervention group and the control groups discontinue the therapy. Furthermore, possible changes of the chronotypes in the course of the study will be defined by the Munich ChronoType Questionnaire (MCTQ).

As alcohol has various negative effects on different blood cells and their functions, we will also take blood samples and assess liver and blood parameters (see Table 2).

**Table 2 T2:** Overview of blood parameters that will be assessed at baseline and at 6-weeks follow-up.

**Liver values**		**Blood cells and other AUD related values**	
**Abbreviation**	**Full name**	**Abbreviation**	**Full name**
GOT	Glutamic Oxaloacetic Transaminase	MCV	Mean Corpuscular Volume
GPT	Glutamate-Pyruvate-Transaminase	Hb	Hemoglobin
GGT	Gamma GT	Vit B12	Vitamin B12
aP	Alkaline Phosphatase	CDT	Carbohydrate-Deficient Transferrin

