## Study Hypotheses and Objectives

Our primary hypothesis is that a regular exposure to *Zeitgebers* stabilizes circadian behavioral rhythms and thereby reduces alcohol consumption and the risk of alcohol relapses in AUD patients. Accordingly, the primary objectives of the study are to determine whether the intervention program DAILY decreases day-to-day variations in behavior and reduces alcohol consumption and the relapse rate in AUD patients compared to those receiving control treatment. Furthermore, we hypothesize that the regular exposure to *Zeitgebers* contributes to the reduction of depressive symptoms and a subjective and physiological well-being in AUD patients, which in turn positively affects the primary objectives of the study. Accordingly, the secondary objective of the study is to ascertain whether the DAILY program supports the surrogate criterions of increased sleep quality, reduced depressive symptoms, increased self-efficacy expectations, and improved blood-values that are associated with harmful alcohol consumption. We also hypothesize, that additional psychoeducation about biological mechanisms in the development of AUD helps participants to complete their current therapy and maintain compliance. Therefore, as exploratory outcomes, we will investigate whether more participants of the intervention group accomplish the DAILY therapy than participants of the control group. Finally, we will assess whether the DAILY intervention has impact on the chronotype of the participants, although it is not a specific aim of our treatment to change it.

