Cognitive behavioral therapy for insomnia (CBT-I) focuses, like parts of DAILY, on a regular sleep schedule, stimulus control, and improved sleep hygiene. Other core components of CBT-I are sleep restriction and relaxation techniques, which are not used in DAILY. CBT-I treatment in AUD patients effectively reduces insomnia, associated negative cognitions, and improves sleep hygiene, but, however, is not successful in changing drinking behavior (78, 79). Apart from sleep problems, AUD patients often suffer from irregular routines throughout the day, including the timing of meals. Thus, in contrast to the focus of CBT-I on sleep improvement, DAILY aims to stabilize the circadian system of the entire body, including clocks in peripheral organs and reward-regulating brain areas, which in our opinion is more likely to improve alcohol outcomes.

In summary, in DAILY we aim to increase stability and regularity of circadian rhythms of AUD patients by creating daily routine schedules which will consider as many endogenous circadian preferences as possible, but also social obligations. Actions whose timing is determined by social constraints will be integrated in the daily routine schedules to make their execution feasible, and their timing is kept the same on all days to create endogenous synchronization. In subjects whose daily routine schedule deviates more than 2 h from endogenous rhythms, light therapy will be used to adjust their chronotype to avoid social jetlag. In this way we obtain a high degree of personalization and can try to create the best possible daily profile for each subject.

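### The Routine Variability Score, a primary outcome, takes in sleep quality, which its minutes-based rule cannot score, and appears to list going to bed twice

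*Protocol article*

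**What the plan says.** Under Measured Outcomes, the article states that "the first primary outcomes of the study are the Routine Variability Score and drinking behavior of each individual test person". The inputs to the score are "bedtime, wake-up time, sleep quality, time of getting-up in the morning, time to go to bed in the evening, lights-off time", followed by "breakfast time, lunch time and dinner time": nine parameters, six about sleep and three about meals.

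The scoring rule is worked through for bedtime only. A weekly average time is formed. "Then the deviation from this average bedtime is calculated in minutes for each day" The deviations are then averaged. "This mean value will be coded according to the magnitude of time variability: 1: 0–15 min", and so on through eleven bands, the last being more than four hours. The article says a separate score can be made in this way for each diary parameter. Scores may be weekly or for the whole survey phase, and sleep and meal scores may also be calculated on their own. No sum, mean or weights are given for joining the parameters into one score.

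Study Hypotheses and Objectives places sleep quality among the secondary aims, as one of "the surrogate criterions of increased sleep quality, reduced depressive symptoms". Measured Outcomes assigns sleep quantity and quality to the PSQI. The diary also collects sleep quality daily (Intervention Group, Week 1), where it is listed with mood and craving as well as the recorded times.

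**The concern.** The score is meant to capture how regular the timing of daily activities is. Two features of the input list do not fit that purpose.

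- **Sleep quality is not a time.** The coding is explicitly "This mean value will be coded according to the magnitude of time variability", and a rating has no deviation in minutes. Whoever computes the score must leave the item out, treat rating points as minutes, or invent a conversion. These choices give different primary outcomes, and the third brings a secondary outcome into the primary one.
- **Going to bed appears under two names.** Bedtime and the evening go-to-bed time read as the same event, and lights-off is close to both. If the items are pooled, one behaviour is counted more than once. If they are analysed separately, one effect can appear as two results.

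The score also serves as a predictor. Data Analysis uses it as the independent variable in linear regression, and as one of several predictors of primary and secondary outcomes in multiple regression. A score that contained a varying sleep-quality component would partly predict itself when the outcome is sleep quality.

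**Working it through.** The article states no total score, weight, sample size or power for this outcome, so there is no figure of its own to reproduce. The inputs are the nine parameters, the minutes rule and the bands, all from Measured Outcomes. The rating scale for sleep quality is not given in the text shown, so a range is used.

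**1. Sleep quality under the stated rule.** For a rating with range R over seven days, the mean absolute deviation is largest when three days lie at one end and four at the other:

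- maximum = 2 × (3/7) × (4/7) × R = (24/49) × R = 0.490 R
- R = 10 (assumed 0–10 scale): 0.490 × 10 = 4.9, inside 0–15, so always code 1
- leaving code 1 requires 0.490 R > 15, that is R > 15 × 49/24 = 30.6
- R = 100 (assumed 0–100 scale): up to 49.0, which could reach code 4 (46–60)

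On any scale narrower than about 31 points the item is a constant. On a wider scale it varies, but the bands would be applied to points rather than minutes.

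**2. What it would measure if it varied.** Take ratings of 2, 3, 4, 5, 6, 7, 8 over a week (illustrative). The mean is 5 and the mean absolute deviation is (3+2+1+0+1+2+3)/7 = 12/7 = 1.71. A patient who rates 2 every day has deviation 0. After any rescaling that made the item informative, the steadily improving sleeper would score as less regular than the uniformly poor one, although better sleep is a secondary aim.

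**3. Overlapping items.** This step assumes an equal-weight mean, which the article does not state.

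| Item set | Items | Meals | Going to bed, including lights-off |
|---|---|---|---|
| As listed | 9 | 3/9 = 33.3% | 3/9 = 33.3% |
| Sleep quality removed | 8 | 3/8 = 37.5% | 3/8 = 37.5% |
| Bed event also counted once, lights-off distinct | 7 | 3/7 = 42.9% | 2/7 = 28.6% |
| Lights-off merged too | 6 | 3/6 = 50.0% | 1/6 = 16.7% |
| Waking and getting up merged too | 5 | 3/5 = 60.0% | 1/5 = 20.0% |

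If lights-off is a distinct event, the two bed items alone carry 2/9 = 22.2% as listed.

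Under the same assumption, a fall of three codes in all three evening items lowers the nine-item mean by (3 × 3)/9 = 1.00. It lowers the six-item mean, where they are one item, by 3/6 = 0.50. A fall of three codes in all three meals lowers the nine-item mean by 9/9 = 1.00 and the seven-item mean by 9/7 = 1.29.

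**The case against.** Several counter-arguments have force.

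- **A constant does no harm to a comparison.** If sleep quality is always code 1, it rescales a mean equally in both groups and cannot bias the contrast or change a ranking. That is correct. The literal reading therefore makes the item useless rather than biasing; the harm arises if someone converts it so that it varies. The stated rule still does not fit the listed input.
- **The diary is not shown.** Supplementary Table 1 may separate the bed items. Lights-off can differ from going to bed, and waking from getting up, so merging all of them could lose information. This stands and limits the fix: only the two bed items read as the same event on the page.
- **The full protocol or an analysis plan may hold a combining rule.** It may, and its absence from an article is not held against the plan.

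A reader might go further and infer that the score misweights regularity, gives meals too little weight and dilutes a real effect on meal timing. The article does not support that. It states no equal-weight composite and no intended weight for meals, and it targets both eating and sleeping times. It already allows separate sleep and meal scores, in which a meal effect would be visible. Even with all three evening items counted as duplicates, going to bed fills three of nine slots, no more than meals. The contrast with CBT-I is also broader than meals: "in contrast to the focus of CBT-I on sleep improvement, DAILY aims to stabilize the circadian system of the entire body".

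Nor does a reversal of patient rankings follow. Take one patient with sleep deviations of 10 min (code 1) and meal deviations of 80 min (code 6), and a mirror patient, with sleep quality at code 1.

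- Nine items: (5×1 + 1 + 3×6)/9 = 2.67 against (5×6 + 1 + 3×1)/9 = 3.78.
- Five items: (2×1 + 3×6)/5 = 4.0 against (2×6 + 3×1)/5 = 3.0.
- Seven items: (4×1 + 3×6)/7 = 3.14 against (4×6 + 3×1)/7 = 3.86.
- Equal sleep and meal halves: (1 + 6)/2 = 3.5 for both.

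The order flips only under the five-item choice, so the reversal comes from the alternative selected.

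**Conclusion.** The point holds as a fault in the definition of a primary outcome. One of the nine listed inputs, sleep quality, cannot be validly scored by the stated rule: it is constant on any rating scale narrower than about 31 points, and otherwise does not measure timing. This rests only on the published text, apart from the assumed scales used for illustration. The bed event appears to be listed twice; that rests on the wording, since the diary is not shown. The shares of up to 33% for going to bed and 33% for meals hold only if the nine items are averaged equally, which is an assumption. No bias between groups, loss of a meal effect or misranking of patients has been shown. For a pilot without formal power calculations this is a modest correction, but worth making because it concerns what a primary outcome measures.

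**What to change.** - Remove sleep quality from the Routine Variability Score and report it separately, as a diary measure beside the PSQI.
- Count bedtime and the evening go-to-bed time once. Keep lights-off, wake-up and getting-up as separate items only if the diary records them as distinct events, and define each in a phrase.
- Report the sleep-timing and meal-timing sub-scores, which Measured Outcomes already permits, alongside any overall score.

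The cost is wording. The diary, visits and data collection stay as they are, and the parameters concerned are already diary items. The change should be settled before the groups are compared on this outcome.

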### Outlook

In future studies, the determination of individual circadian traits will be optimized in two approaches. First, outpatients will be included because these patients most likely organize their day following primarily their endogenous clock compared to inpatients who are integrated into the daily structures of the clinic. Second, we will also use actigraphy on the one hand to receive a more objective measure of regularity of rest-activity rhythms and on the other hand because filling out diaries carries a high risk of non-compliance and therefore a high risk of data gaps.

In recent years, great progress has been made in the development of machine learning methods for the evaluation of circadian variables of actimeter data, with which for example the circadian phase can be determined (80–83). In this regard, a newly developed DLMO prediction model based on actimetry data, which can be used to quantify circadian misalignment, seems particularly useful to quantify irregularities in circadian rhythms and behavior (84). Therefore, the application of actimeters and the use of mathematical algorithms for analysis will be part of future and more comprehensive studies. The results obtained can in turn be used to adjust and refine daily structure plans of the individual participants of our second study cohort.

Beyond that, we will try to identify times of the day when alcohol cravings are particularly high. Knowing about these times, we will encourage the patients to use these hours to have recourse on learned skills (doing sports, contacting close persons etc.) in order to overcome this period more successfully.

The overall goal of this and more extended future studies is the development of an accompanying therapy for AUD patients that is uncomplicated in its use and easy to implement in the clinical routine. This therapy should enable AUD patients to bring more regularity and structure into their everyday life and thus to strengthen their circadian system. This, in turn, may be a critical component in overcoming alcohol withdrawals and in preventing relapses more successfully.

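### The scoring rule for the Routine Variability Score omits that deviations are absolute, includes an item that is not a time, and drifts toward regularity when diary days are missing

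*Protocol article*

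**What the plan says.** Measured Outcomes in the protocol article gives the score its rank: "the first primary outcomes of the study are the Routine Variability Score and drinking behavior of each individual test person". It then sets out the calculation step by step, with bedtime as the example:

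- Reference point: "For the period of 1 week, the average bedtime will be calculated".
- Daily deviation: "Then the deviation from this average bedtime is calculated in minutes for each day".
- Aggregation: "These deviations are summed up and the mean value is calculated".
- Coding: "This mean value will be coded according to the magnitude of time variability: 1: 0–15 min, 2: 16–30 min", and so on up to code 11 for more than 4 hours. There is no code 0.

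The parameters include "bedtime, wake-up time, sleep quality, time of getting-up in the morning, time to go to bed in the evening, lights-off time", followed by the three meal times. Scores may be formed by week or over the whole diary period. No minimum number of diary entries is given.

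Data Analysis uses the score as the independent variable of a linear regression that ignores group, and again as a predictor in multiple regressions. It states a general rule that missing data are imputed from what is available, without saying whether this covers single diary days. On diaries, Outlook says that "filling out diaries carries a high risk of non-compliance and therefore a high risk of data gaps".

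**The concern.** There are three difficulties, in order of firmness.

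1. Deviations from a person's own mean sum to zero by construction. A rule that averages them without taking absolute values carries no information about variability.
2. Sleep quality has no deviation in minutes, so the stated rule cannot be applied to it. Restoring the word absolute does not repair this.
3. A mean absolute deviation around the person's own mean depends on how many days were recorded. Fewer entries pull the mean toward those entries and shrink the score, so an incomplete diary looks more regular than a complete one from the same person.

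The third point could affect the comparison of arms. Study Hypotheses and Objectives asks whether more intervention than control participants complete the programme. If so, and if control diaries are therefore sparser, controls would look falsely regular and a true effect on regularity would be diluted. If gaps fall the other way, the bias favours the intervention. In the group-independent regression, people with sparse diaries would be placed too low on the score whatever their true regularity.

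**Working it through.** The article states no worked score, standard deviation or sample size, so there is no figure of its own to reproduce. The rule and bands come from Measured Outcomes. The day-to-day SD is an assumption, shown over 20 to 120 min.

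**Step 1: the rule as printed.** For daily times x₁…xₙ with mean x̄, Σ(xᵢ − x̄) = Σxᵢ − n·x̄ = 0. An illustrative week of bedtimes is 22:00, 23:00, 22:30, 24:00, 01:00, 21:30, 23:00, with mean 23:00. The deviations are −60, 0, −30, +60, +120, −90 and 0 min.
- As printed: sum 0, mean 0 min, code 1.
- Absolute: (60 + 0 + 30 + 60 + 120 + 90 + 0)/7 = 360/7 = 51.4 min, code 4.

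**Step 2: absolute deviations and number of entries.** For independent normal times with standard deviation SD, and gaps unrelated to the times themselves:

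E(mean absolute deviation) = SD · √(2/π) · √((n−1)/n)

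The ratio to a 7-entry week is √((n−1)/n) / √(6/7), which does not depend on SD. For example, at n = 3 it is 0.8165/0.9258 = 0.88. At SD 60 min, SD·√(2/π) = 47.9 min. The minutes and ratios below come from the formula; mean code and chance of code 1 come from 200,000 simulated weeks.

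| Entries | Expected min (SD 60) | Ratio to 7 entries | Mean code | Chance of code 1 |
|---|---|---|---|---|
| 7 | 44.3 | 100% | 3.46 | 0.4% |
| 5 | 42.8 | 97% | 3.36 | 2.1% |
| 4 | 41.5 | 94% | 3.27 | 4.8% |
| 3 | 39.1 | 88% | 3.11 | 11.0% |
| 2 | 33.9 | 76% | 2.78 | 27.5% |
| 1 | 0 | 0% | 1.00 | 100% |

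Over SD 20 to 120 min, the chance of code 1 runs from 71% down to 14% with 2 entries, and from 55% down to essentially 0% with 7.

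**Step 3: what a correction achieves.** Multiplying by √(n/(n−1)) makes the expected minutes SD·√(2/π) for every n ≥ 2. It does not restore precision. With n = 2 the corrected score is |x₁ − x₂|/√2, which is distributed as |N(0, SD)|. At SD 60 the chance of code 1 is then P(|Z| ≤ 15/60) = 20%, still far above the 7-entry figure. A minimum number of entries is therefore needed as well.

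**Step 4: one score over the whole period.** Weeks 3–6 notes that many patients are discharged or transferred in this phase. Take someone perfectly regular whose bedtime moves once, by 90 min, at the midpoint. The overall mean lies 45 min from every day, so the score is 45 min, code 3. If the move falls between two weeks, every weekly score is 0 min, code 1.

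**The case against.** The text never calls the deviations signed. The coding sentence speaks of magnitude, and the non-negative bands extend beyond 4 hours, which fits only absolute deviations. The intended meaning is recoverable, and an analyst would very likely compute it. This stands: a reader might infer that the primary outcome is zero for everyone, but the bands do not support that. What remains is a misprint in a step-by-step definition, not a detail left to another document.

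A reader might also infer that sparse diaries score as perfectly regular. That is certain only for a one-entry week. With 5 entries the shortfall is about 3%, and a week with no entries yields no score at all.

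A minimum-entries rule may stand in a fuller document, and the imputation rule may cover diary days. Both are possible. Imputation does not settle the matter unless its method is given: filling four missing days with the mean of three recorded ones adds four zero deviations and multiplies the score by 3/7.

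Four further inferences rest on assumed handling or on the diary form, which is not shown:
- That bedtimes are averaged as raw clock values. A week of 23:30, 00:15, 23:00, 00:30, 23:45, 00:00 and 23:30 would then average 13:30 with a mean absolute deviation of 681 min, against 24 min measured across midnight. Nothing prescribes that calculation.
- That the two bedtime items record the same event. Their difference is unexplained, but duplication cannot be verified.
- That a skipped meal enters as missing. No coding is stated.
- That the test week is pooled with the application phase. The whole-period option does not define its span.

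Finally, this is a pilot, and drinking behaviour stands beside the score as a primary outcome. That lowers the stakes but does not make the rule right.

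**Conclusion.** The scoring rule is misstated in two respects that need no assumption: it omits absolute values, and it applies a minute-based coding to sleep quality. Both should be corrected before any score is computed.

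The bias from missing days is real but graded: about 3% with 5 of 7 entries, 12% with 3, 24% with 2, and a guaranteed best code with 1. These percentages assume independent, normally distributed times and gaps unrelated to irregularity. They do not depend on the SD, whereas the minutes and code probabilities do. The direction and size of any effect on the arm comparison are unknown, because the article does not say how gaps will be distributed between arms. The documents do not support a claim that the outcome is unusable once the wording is repaired.

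**What to change.** In the scoring text:

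- Define each parameter's weekly score as the mean absolute deviation in minutes from the person's weekly mean, with clock times measured continuously across midnight.
- Remove sleep quality from the minute-coded parameters.
- State how the bedtime item differs from the evening going-to-bed item, or merge them.
- Treat a parameter-week below a prespecified minimum number of entries as missing, and say whether imputation applies to diary days.
- Multiply the remaining scores by √(n/(n−1)) before coding. An SD with divisor n−1 is an alternative. It lessens the dependence on n without removing it, and because it is a different quantity from a mean absolute deviation the bands would need review.
- For the group comparison, use the average of the weekly scores in the 4-week application phase, so that one shift at discharge is not counted as day-to-day variability.

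The cost is confined to scoring, and no new data are needed. Some parameter-weeks become missing instead of falsely regular. The corrected minutes depart slightly from the cited coding: for a full week the factor is √(7/6) = 1.08. Uncorrected scores can be reported alongside for comparison.
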